### Primary Endpoints

The primary endpoints are the prevalence and incidence of symptoms of PTSD, depression, anxiety, and alcohol use disorder. Since we will not be able to establish diagnoses through mental healthcare experts (psychiatrists or psychologists) according to the International Classification of Disease (ICD)- 10/11, or the Diagnostic and Statistical Manual of Mental Disorders (DSM)- 5, we rely on commonly used, standardized questionnaires which we selected following a systematic selection process [18]. For the four mental health conditions of interest, we identified potential instruments and compared them against our selection criteria: (a) should have strong psychometric properties (construct validity, internal consistency reliability, test-retest reliability, and ability to detect change over time) to capture symptoms; (b) estimates of sensitivity and specificity are available (c) can be implemented in digital surveillance (i.e., can be completed independently by participants); (d) are available in the Ukrainian language; (e) are appropriate in the context of the war in Ukraine; (f) have established cut-offs for the presence or likely presence of the four conditions of interest; (g) are or have been used in other population-based studies; (h) are short in duration or low burden to complete; (i) have been previously used in Ukraine. Instruments were discussed and final decisions made at an international working group meeting held in Zurich in Spring 2023.

Based on the criteria mentioned above, we selected the Posttraumatic Stress Disorder Checklist (PCL-5) for the assessment of PTSD, Patient Health Questionnaire (PHQ-9) for depression, generalized anxiety disorder 7 (GAD-7) for anxiety, and Alcohol Use Disorders Identification Test (AUDIT) for the alcohol use disorder. References for each of the instruments regarding the validation of psychometric properties (in a general non-Ukrainian population), the translation process into Ukrainian, and validation and/or utilisation in the Ukrainian population are provided in Table 1. Furthermore, the selected instruments are aligned with those used by the Global Burden of Disease (GBD) from The Institute for Health Metrics and Evaluation.

**TABLE 1 T1:** Mental Health Assessment of the Population, Switzerland, 2024

Instrument	Sensitivity %/Specificity % (score of instrument as cut-off)	Psychometric properties	Translation process	Validation/utilisation in Ukraine
PCL-5	94/94 (31)	Geier et al. [19] Karachevskiy et al. (2016) [20]	Roberts et al. (2019) [5]	Roberts et al. (2019) [5] ^a^ Karachevskiy et al. (2016) [20]
PHQ-9	88/88 (10)	Kroenke et al. (2001) [21]	Roberts et al. (2019) [5]	Roberts et al. (2019) [5] Osokina et al. (2022) [22] ^b^
GAD-7	89/82 (10)	Spitzer et al. (2006) [23]	Roberts et al. (2019) [5]	Roberts et al. (2019) [5] Osokina et al. (2022) [22] Ochnik et al. (2021) [24] ^b^
AUDIT	65/85 (5)	Moehring et al. (2019) [25]	Ramachandran et al. (2019) [7]	Ramachandran et al. (2019) [7] ^c^ Ministry of Health Ukraine (2014) [26] ^d^ Decyk et al. (2013) [27] Fitkalo (2023) [28]

*Note*:

^a^
Good reliability and construct validity in a Ukrainian sample.

^b^
Utilisation in a Ukrainian sample, no report on validation.

^c^
Good reliability in a Ukrainian sample.

^d^
Approval and recommendation of the Ukrainian version in a clinical context (alcoholic hepatitis) as a screening tool for measuring alcohol abuse.

Standardized instruments are often used for screening purposes with thresholds for the presence of a specific mental health condition that are optimized for sensitivity. As a consequence, prevalence is often overestimated when not corrected for accuracy [18]. Therefore, we will correct prevalence estimates for misclassification as described below.

We consulted systematic reviews [29–32] to assist us in identifying studies in the available literature that provide estimates of diagnostic accuracy in samples that are comparable to our study population. We selected estimates of sensitivity and specificity from studies if, whenever available, the studies included a population-based sample, used structured diagnostic interviews as reference standard, had a sample size of >100 and >50 positive cases, showed mean values that are comparable to those in our population (based on participants included up to June 30, 2024), and where we deemed the study population similar to our study population. We favoured primary studies over meta-analyses, because we are better able to assess similarity between our population and a single well-characterized sample than to compare our population with the heterogeneous aggregate of samples that underly a meta-analysis.

For the PHQ-9 we chose a cut-point of >=10 and assume a sensitivity of 0.88 and specificity of 0.88, as reported by Kroenke and colleagues [21]. The cut-point for the GAD-7 is >=10, the assumed sensitivity is 0.89 and specificity is 0.82 as reported by Spitzer et al. [23]. In the case of the AUDIT, we believe that the most applicable estimate of diagnostic validity was provided by Moehring et al. [25] based on a general population study in Germany. They observed a very similar AUDIT score distribution to the one in our population and, given a cut-point of >=5, reported a sensitivity of 0.65 and specificity of 0.85. The most applicable estimate for the diagnostic validity of the PCL-5 was provided by Geier et al. [19] which found that a cut-point of >=31 resulted in a sensitivity of 0.94 and a specificity of 0.94.

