### Study Objectives

The main goal of the MAP program is to implement an agile, digital surveillance of public mental health in adult people living in different parts of Ukraine and in Ukrainian refugees living in the Canton of Zurich, Switzerland. The specific objectives are: (1) to determine the prevalence of symptoms of PTSD, depression, anxiety, and alcohol use disorder (a) at the beginning of the surveillance, and (b) up to at least 2 years; (2) to determine short-term and long-term temporal developments of mental health in the Ukrainian general population (in Ukraine and in the Canton of Zurich) and subgroups defined by age and level of war-related exposure; (3) to assess how mental health impacts general health and healthcare seeking behaviour; and (4) to assess needs, preferences, barriers, and facilitators for mental healthcare services of the Ukrainian general population and subgroups.

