### Statistical Analysis Plan and Sample Size Calculation

#### Statistical Methods

We will use medians and interquartile ranges or absolute numbers and percentages for the descriptive analyses. For prevalence estimates, there is the risk of overestimation if based on raw numbers since the cut-offs of instruments to classify into mental health condition (yes, likely) are optimized for sensitivity and screening for mental health conditions and thus include varying extent of false-positives. A recent systematic review indicated that prevalence estimates based solely on standardized instruments are about double as high as prevalence estimates based on standardized diagnostic interviews [18]. We will take this challenge into account in different ways: First, we will provide prevalence estimates and 95% credible intervals using a Bayesian logistic regression model adjusted for age-group and cluster of oblasts taking sensitivity and specificity of the instruments, as described above, and their uncertainty into account [33, 34].

We will conduct these analyses for the entire study population and also estimate prevalence of the four mental health conditions for subgroups as defined by cluster of oblasts (see above), age group and sex. The same applies to the analyses of aims 2 (impact of mental health on general health and healthcare seeking behaviour) and 3 (needs, preferences, barriers, and facilitators for mental healthcare services) where it is critical to gain an understanding of differences across subgroups. To assess factors (cluster, age, sex, sociodemographic variables, war-related experiences) associated with alcohol use disorder, abuse, anxiety, depression, or PTSD as well as with general health and healthcare seeking behaviour and needs, preferences, barriers, and facilitators for mental healthcare services we will use regression models while carefully adjusting for potential confounders. We will also consider clustering approaches to identify subgroups of the population with specific mental health burden and healthcare and social support needs. We will conduct all analyses in R, using the most current version at time of analysis https://www.r-project.org/.

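### Incidence is a primary endpoint, but the stated misclassification correction covers only prevalence, so estimated incidence could be largely test error, especially for anxiety and alcohol

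*Protocol article*

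**What the plan says.** All references are to the protocol article.

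- **Endpoint.** Primary Endpoints: "The primary endpoints are the prevalence and incidence of symptoms of PTSD, depression, anxiety, and alcohol use disorder". The Abstract says the same.
- **Correction.** The same section explains that screening thresholds inflate prevalence and concludes: "Therefore, we will correct prevalence estimates for misclassification as described below". Statistical Methods then gives the remedy: "we will provide prevalence estimates and 95% credible intervals using a Bayesian logistic regression model adjusted for age-group and cluster of oblasts", with the accuracy of the instruments and its uncertainty carried into the model.
- **Accuracy values.** Primary Endpoints gives them for each instrument. For depression: "For the PHQ-9 we chose a cut-point of >=10 and assume a sensitivity of 0.88 and specificity of 0.88". For the PCL-5, "a cut-point of >=31 resulted in a sensitivity of 0.94 and a specificity of 0.94". For the GAD-7 they are 0.89 and 0.82, and for the AUDIT 0.65 and 0.85.
- **Objectives.** Study Objectives lists four. The second reads: "2) to determine short-term and long-term temporal developments of mental health in the Ukrainian general population". Effects on general health and care seeking come third, and care needs fourth.
- **Aims in the analysis.** Statistical Methods refers to "aims 2 (impact of mental health on general health and healthcare seeking behaviour) and 3 (needs, preferences, barriers, and facilitators for mental healthcare services". These are objectives 3 and 4 under other numbers, so objective 2 is not mentioned there.
- **Other analyses.** For associated factors, "we will use regression models while carefully adjusting for potential confounders"; clustering approaches are also mentioned. Sample Size Considerations and Calculation works from the precision of prevalence alone.

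**The concern.** The authors accept that a positive score is not a case and that raw prevalence is therefore too high. The same error affects incidence, and can affect it more. Someone without the condition who scores below the cut-off at one wave and falsely above it at the next looks like a new case. So does someone with the condition who is missed at one wave and detected at the next. When true onset over 3 months is uncommon, these two streams can match or exceed the true new cases.

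Followed as written, the article would correct one half of its primary endpoint and leave the other half exposed to the bias it has just described. The bias also differs by instrument, so a comparison of incidence across the four conditions would partly reflect questionnaire accuracy.

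**Working it through.** **The article's own calculation.** Prevalence 40%, ±5 points, 95% confidence: n = 1.96² × 0.40 × 0.60 / 0.05² = 368.8, so 369. With 15% attrition, 369 / 0.85 = 434.1, so 435. Over 12 strata, 435 × 12 = 5,220. All three agree with the article. None concerns incidence.

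**Inputs from the article.** Se and Sp from Primary Endpoints; expected prevalence π from Sample Size Considerations and Calculation.

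| | Se | Sp | π |
|---|---|---|---|
| PTSD (PCL-5) | 0.94 | 0.94 | 0.40 |
| Depression (PHQ-9) | 0.88 | 0.88 | 0.25 |
| Anxiety (GAD-7) | 0.89 | 0.82 | 0.25 |
| Alcohol (AUDIT) | 0.65 | 0.85 | 0.15 |

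**Inputs not in the article.** True 3-month incidence i, quarterly remission r, and the share ρ of error that persists within a person between waves. These are assumed and shown as ranges.

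**Step 1: nobody changes.** Apparent incidence among those negative at the first of two waves is

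(1 − ρ) × [(1 − π)·Sp·(1 − Sp) + π·(1 − Se)·Se] / [(1 − π)·Sp + π·(1 − Se)].

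With ρ = 0:

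- PTSD: (0.0338 + 0.0226) / 0.588 = 9.6%
- Depression: (0.0792 + 0.0264) / 0.690 = 15.3%
- Anxiety: (0.1107 + 0.0245) / 0.6425 = 21.0%
- Alcohol: (0.1084 + 0.0341) / 0.775 = 18.4%

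| Apparent 3-month incidence, no true change | PTSD | Depression | Anxiety | Alcohol |
|---|---|---|---|---|
| ρ = 0 | 9.6% | 15.3% | 21.0% | 18.4% |
| ρ = 0.5 | 4.8% | 7.7% | 10.5% | 9.2% |
| ρ = 0.8 | 1.9% | 3.1% | 4.2% | 3.7% |

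**Step 2: allow true onset and remission.** Apparent new cases then have four sources:

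- a, non-cases testing falsely positive: (1 − π)·Sp·(1 − i)·(1 − Sp)·(1 − ρ)
- b, true new cases detected: (1 − π)·Sp·i·Se
- c, existing cases missed at the first wave: π·(1 − Se)·(1 − r)·Se·(1 − ρ)
- d, missed cases that remit and then test falsely positive: π·(1 − Se)·r·(1 − Sp)

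The error share is 1 − b / (a + b + c + d). Assume r = 10% per quarter and stable prevalence, so i = r·π / (1 − π), which gives 6.7%, 3.3%, 3.3% and 1.8%. For PTSD with ρ = 0: a = 0.0316, b = 0.0353, c = 0.0203, d = 0.0001, and 1 − 0.0353 / 0.0874 = 60%.

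| Share of apparent new cases that is test error | PTSD | Depression | Anxiety | Alcohol |
|---|---|---|---|---|
| ρ = 0 | 60% | 84% | 88% | 94% |
| ρ = 0.5 | 42% | 72% | 78% | 89% |
| ρ = 0.8 | 23% | 51% | 59% | 77% |

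**Step 3: a less favourable case for the concern.** With r = 10%, ρ = 0.8 and true incidence 5% per quarter in all four conditions, the shares are 29%, 41%, 49% and 54%.

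**The case against.** **This is a condensed article.** The definition of incidence, the at-risk set and the longitudinal model may stand in a fuller plan that is not shown. The article says it will handle misclassification in several ways and spells out only the first, which fits abridgement. This stands as far as it goes: the absence of a multi-wave model here is not in itself an error. What remains is a mismatch in the text. The article names a bias, states a remedy for one half of its primary endpoint, and numbers its aims so that the temporal objective falls out.

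**The renumbering may be a slip.** It may also reflect a merging of objectives 1 and 2, since objective 1 already covers prevalence over at least 2 years. That is possible. It shows a text to be realigned, not an analysis deliberately dropped.

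**Crossing counts are not announced.** Nothing says incidence will be computed from raw crossings of the cut-off. The figures above therefore show what happens without a correction, not what the investigators have said they will do.

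**A reader might infer more than the article supports:**

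- *That most apparent new cases must be test error.* This depends on true incidence and on error dependence between waves, and the article gives neither. Errors by one person on one questionnaire are plausibly positively correlated, so independence is the upper end. In the stable-prevalence scenario the inference fails for PTSD once half the error persists.
- *That the public platform would show spurious onset and remission.* The article promises prevalence and trajectories for the population and subgroups, which corrected prevalence over time would satisfy.
- *That the association analyses are attenuated.* The article specifies neither the outcome scale of those regressions nor whether the accuracy correction enters them.

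**Conclusion.** The point holds as an inconsistency with a material consequence. Without correction, the instruments alone would produce an apparent 3-month incidence of roughly 10% to 21% with independent errors, and roughly 2% to 4% even if 80% of the error is constant within a person. These figures rest on the article's accuracy values and expected prevalences, plus an assumed range for error dependence.

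How much of the observed incidence would be error depends further on assumed onset and remission. With stable prevalence and 10% quarterly remission, the share runs from 94% down to 77% for alcohol, 88% to 59% for anxiety, 84% to 51% for depression and 60% to 23% for PTSD as the error correlation goes from 0 to 0.8. Incidence could therefore be largely test error, most clearly for alcohol and anxiety and least for PTSD. Even the lowest share is too large to ignore in a primary endpoint.

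**What to change.** In Primary Endpoints and Statistical Methods, choose one of two courses.

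1. **Extend the sensitivity and specificity correction to incidence.** Define who is at risk, what counts as a new case and over what interval. Estimate incidence with a multi-wave model that carries the same accuracy uncertainty as the prevalence model. A latent transition or hidden Markov model is one option among several. Report results over a stated range of error dependence between waves.
2. **Remove incidence from the primary endpoints** and report change in misclassification-corrected prevalence over the waves.

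In either case, renumber the aims in Statistical Methods to match Study Objectives and name the analysis that serves objective 2. If a fuller plan already holds the longitudinal model, a sentence and a reference to it would do.

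No new data are needed. The cost is more analysis work and wider intervals for incidence, which will also depend visibly on the assumed error dependence.

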### Secondary Endpoints

Secondary endpoints include participants’ health-related quality of life (as measured by the European Quality of Life 5 Dimensions (EQ-5D-5L) instrument and the visual analogue scale [EQ-VAS]), experiences of somatic distress syndrome (measured with PHQ-15). To measure social isolation and social integration we adapted questions taken from the Swiss Health Survey (2022). Final English and Ukrainian versions of the Swiss Health Survey questions were developed through a process of duplicate independent translations followed by creating consensus-derived, culturally sensitive final versions. We use the Short Warwick-Edinburgh Mental Wellbeing Scale (SWEMWBS) to assess the mental wellbeing of the population. Needs, preferences, barriers, and facilitators for mental health services will be assessed by free-text questions.

Primary endpoints will be collected at each assessment timepoint. Secondary endpoints will be collected both at baseline and during follow-up. Follow-up assessment of secondary endpoints will be distributed over time (e.g., some at 3 months, some at 6 months), to shorten the length of follow-up assessments. Assessment of specific secondary endpoints at flexible time points depending on current events in Ukraine will also be considered. Prior to the final roll-out of the baseline and repeated assessments, we will conduct a small pilot study and focus group discussion with a diverse group of participants, to ensure the appropriateness of the assessments to the Ukrainian context and to the experiences of the population.

### Project Population, Inclusion, and Exclusion Criteria

#### MAP-U

The target population of MAP-U is adults (age 18 and over) living in Ukraine. The source population is adults registered as residents in 10 selected oblasts from all parts of the country that are affected differently by the war. Of the 27 oblasts of Ukraine, the 3 occupied oblasts (Figure 1; Luhansk, Crimea, Donetsk) are currently excluded from consideration. Specifically, the oblasts of Ukraine were randomly selected according to a geographical criterion of two oblasts from each region: Northern Ukraine (Zhytomyr, Rivne); Eastern Ukraine (Sumy, Kharkiv); Southern Ukraine (Mykolaiv, Kherson); Western Ukraine (Lviv, Chernivtsi); Central Ukraine (Kyiv, Dnipropetrovsk).

**FIGURE 1 F1:**
[figure not shown]
Mental Health Assessment of the Population, Ukraine 2024. Note. ^1^ in accordance with the Resolution of the Cabinet of Ministers of Ukraine dated October 14, 2022, No. 1159 “On approval of the Procedure for the development, holding of public discussion, approval of programs for the comprehensive restoration of the region, the territory of the territorial community (its parts), and making changes to them.” Access mode: https://zakon.rada.gov.ua/laws/show/1159-2022-%D0%BF#Text). Date of assessment: 15 June 2024.

Because of the unstable situation in specific oblasts, we decided not to focus on individual oblasts for the analyses but on regional clusters of oblasts, defined by i) level of proximity to the hostilities zone/border with the aggressor = country-aggressor Russian Federation ii) consequences of the full-scale Russian invasion - level of destruction and loss of life; iii) geographical factors.

Cluster North-West (Rivne, Lviv, Chernivtsi oblasts): North-western Ukraine. These oblasts are remote from the hostilities zone and have low security risks due to their proximity to the EU border. There were no direct hostilities in these territories; therewas no large-scale destruction of infrastructure or housing due to hostilities; there has been significant population movement to this region.

Cluster Central (Zhytomyr, Kyiv, Dnipropetrovsk oblasts): Central Ukraine. These oblasts are far from the border with the aggressor and have medium security risks. Part of the territory experienced hostilities in the first months of the full-scale invasion; some areas were temporarily occupied or surrounded; there was destruction of infrastructure and housing due to hostilities and/or shelling.

Cluster South-East (Sumy, Kharkiv, Mykolaiv, Kherson oblasts): South-eastern Ukraine. These oblasts are close to the hostilities zone and have high security risks due to their proximity to the border with the aggressor. Most of the territory experienced hostilities, which are currently ongoing; a large part of the territory was temporarily occupied, and some settlements remain under occupation; significant destruction of infrastructure and housing stock due to hostilities and/or shelling is present; there has been mass emigration of the population to other regions and/or countries and a sharp deterioration in the level of socio-economic development.

Participants from these oblasts will be selected by an age-stratified (18–24, 25–44, 45–64, and 65+ years of age) random sample based on a database provided to the Center for Social Research by the State Statistics Service of Ukraine.

Inclusion criteria for the random sampling: adults (aged ≥18 years) who are residents of the participating oblasts as specified above, providing informed consent and are able to complete the surveys (available in Ukrainian) online or by phone interview.

Excluded from the MAP-U study are individuals who cannot be reached on multiple attempts and those who are in military service and perform combat missions as part of the territorial defence, the armed forces of Ukraine or other military formations.

#### MAP-Z

The target population of MAP-Z is adult Ukrainians who fled from Ukraine and currently live in the canton of Zurich. The source population is Ukrainians registered with refugee status S in the canton of Zurich and the study population consists of a random selection of this group of persons conducted by the Swiss Federal Statistical Office (FSO).

Inclusion criteria for the random, age-stratified (same age categories as for MAP-U) sampling are adults (aged ≥18 years) from Ukraine with refugee status S residing in the Canton of Zurich, providing informed consent and able to complete the surveys (available in Ukrainian) online. Exclusion criteria are individuals who cannot be reached on multiple attempts.

For the control group, adults from the general population of the Canton of Zurich will be randomly selected from the resident registry by the Swiss FSO, again age-stratified (same age categories as for MAP-U).

Inclusion criteria for the random sampling are adults (aged ≥18 years) residing in the Canton of Zurich with either Swiss citizenship or residence permit B or C, providing informed consent and able to complete the surveys (available in German) online.

